
|  | Phone Screener | Base | Every 30 days | CYCLE 6 | CYCLE 13 | Claims |
| --- | --- | --- | --- | --- | --- | --- |
| Age, gender, race, ethnicity (5) | X |  |  |  |  |  |
| Exclusion (smoking amount, Internet access, asthma history, English fluency)(10) | X |  |  |  |  |  |
| Contact and payment information (13) | X |  |  |  |  |  |
| Demographics, height, weight, QOL (14) |  | X |  |  | X |  |
| Asthma Control Test (5) |  | X |  | X | X |  |
| Asthma Control and Quality of Life (11) |  | X |  | X | X |  |
| Health Conditions (14) |  | X |  |  |  |  |
| Patient Satisfaction Questionnaire (19) |  | X |  |  | X |  |
| Patient Involvement (5) |  | X |  |  | X |  |
| Health Literacy (2) |  | X |  |  | X |  |
| Internet Use (29) |  | X |  |  | X |  |
| Asthma Counseling (5) |  | X |  |  | X |  |
| Newest Vital Sign (8) |  | X |  |  |  |  |
| CC Condition Pre-Use Questions (27) |  | X | X* |  | X |  |
| IC Condition Pre-Use Questions (16) |  | X | X* |  | X |  |
| Emergency department visits |  |  |  |  |  | X |
| Medication use and adherence |  |  |  |  |  | x |
| Outpatient provider visits for asthma |  |  |  |  |  | X |
| Adverse events |  |  |  | X | X |  |
| Satisfaction with Intervention |  |  |  |  | X |  |
| Pregnancy Question | X** | X** | X** | X** | X** |  |

* depending on condition randomized to, each subject will complete either the CC or IC questions

** asked to women of child bearing potential only

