Asthma-Related Emergency Department Visits: Improvements in asthma control can decrease future use asthma-related emergency room visits, so we will measure asthma-related emergency department visits 6,100,101. Claims data are valid measures, and superior to other means, such as self-report, for measuring asthma-related emergency department visits. 102,103. Highmark will send us claims data, at the end of the study, which will identify asthma-related emergency department claims. This is data that is already being analyzed by Highmark, in ways that are standardized by the National Committee for Quality Assurance (NCQA), for reporting the quality of care delivered to patients with asthma 7. In the NCQA reporting, asthma-related emergency department visits are one way to identify patients with persistent asthma 7. We will take advantage of that reporting mechanism in the current study.

Asthma Control and Quality of Life: We will use questions about asthma control and quality of life from the National Asthma Survey, from the CDC and published by Halterman and colleagues (Halterman, Aligne et al. 2000). The instrument identifies several aspects of asthma control and how it impacts quality of life, including days with symptoms, days symptom-free, emergency room visits, urgent doctor visits, asthma attacks, severity of asthma attacks and the degree to which asthma impairs function. It is not clear how many of these questions are validated, but they are used as outcome studies in a great number of asthma clinical trials and have strong face validity and national norms is helpful. Drs. [name], [name] and [name] are working on the adult version of the Halterman paper, using the data from the NAS.

**Mediating Variables:** For our purposes, mediating variables are those that the intervention will attempt to modify in order to bring about a change in asthma control and quality of care for asthma. We will examine variables that have been associated with asthma control and quality of care for asthma and those that have been targeted by the intervention and therefore may mediate the effect of the intervention on the above outcome variables. We hypothesize that each of these variables will mediate the effect of the intervention.

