### 7. Statistics and sample size justification

Sample size considerations focus on the primary hypothesis posited in the Specific Aims section. The major research goal is to determine the efficacy of having patients use the asthma module of the interactive website, for a period of 12 months, for improving asthma control. The primary outcome will be asthma control, based on the Asthma Control Test (ACT), a valid and reliable 5-question self-report measure of asthma control. 98-100. We chose to power the study based on asthma control, as it is a powerful predictor of emergency department visits, activity limitations and missing days of work due to asthma 6,100,130, and it is a central goal in both Healthy People 2010 as well as in the 2007 NAEPP Guidelines 26,131. We chose not to power the study on improving the use of controller medications, such as inhaled corticosteroid use, as the rates of use of these medications has increased greatly over the past decade, which would lead to a ceiling effect 7. Despite the broad use of these controller medications, however, asthma control rates are still in the 50% range, so we will not suffer from such a ceiling effect 5. Our estimated baseline rate of 55% is based on two studies of asthma control in similar groups of insured patients that both showed asthma control rates in the 50% range 5,6. For example, Schatz and colleagues observed that 48.4% of 570 insured adults with asthma had an Asthma Control Test (ACT) score of less than 20, the same measure of asthma control that we are using in the current study 5. Vollmer and colleagues reported that 48% of 5,181 insured adults with asthma reported good asthma control, using a slightly different measure of asthma control, the Asthma Quality of Life Questionnaire 6. We expect a slightly higher baseline control rate, as patients who volunteer for clinical trials tend to be healthier than those who do not 132. This expected effect size is based on a meta-analysis by Stone and colleagues that examined the efficacy of reminders, given to patients, on rates of adult immunization and cancer screening services 16. Patient reminders, similar to what we plan to use in the current study, significantly increased immunizations (odds ratio, OR=2.5), mammography utilization (OR=2.3), cervical cytology screening (OR=1.7) and colon cancer screening (OR=2.8). These effect sizes are consistent with reviews by other investigators 23,50,133. In the current study, we will be powered to detect an effect size that translates to a relative risk of 1.3 (0.70 /0.55) and odds ratio of 1.9. We chose this conservative effect size to address the fact that we are not examining a process of care but an outcome of care. While we expect the intervention to lead to increases in the number of controller medications used, additional medications do not always help patients. Also, we need to be sensitive to the possible differences in efficacy between interventions to increase adult preventive services (e.g., pap testing) and studies such as ours that seek to change chronic disease management practices. We considered powering on a numerical change in the Asthma Control Test (ACT), our main outcome measure, but chose not to do this as there is less consensus about what represents a meaningful change in the ACT than there is about what represents appropriate asthma control 5,98. We will, however, analyze changes in the ACT as a continuous variable, in our secondary analyses. Formulas based on the chi-square test were used to derive sample size calculations from the following assumptions. We assume a type I error rate (alpha) of 5% (0.05), 80% (0.80) power, and a two-tailed test, which allows us to detect significant differences in either direction. We expect a 12-month retention rate of 80%, although we believe that our procedures will substantially minimize the likelihood of attrition. We considered randomizing providers but felt that, given the number of providers in the two geographical areas, it was very unlikely that a physician would have more than one subject enrolled in the study. We will, however, track the name of the asthma care provider, so that we can include this variable in a sensitivity analysis, to be certain that adding this variable does not change the conclusions of the data analyses. In order to achieve 80% power to detect a difference of 70% vs. 55% between intervention and control group, we will need to randomize 408 patients into the two conditions at baseline. This assumes that no more than 20% are lost to follow-up at 12 months, leaving no fewer than 326 subjects available for analysis at the end of the study. We do concede, however, that smaller differences in asthma control may be clinically important, particularly on a population level. To power the study on a 10% difference in asthma control, however, we would have needed to recruit 940 subjects, which we felt would unnecessarily increase the cost and complexity of the study.

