Secondary analyses: The secondary hypotheses, taken from the Specific Aims, are that subjects in the IC will have fewer asthma-related emergency department visits, greater gains in their asthma-related quality of life, greater increases in their controller-to-reliever medication ratio, greater satisfaction with asthma treatment and greater adherence to their asthma controller medications, after 12 months, than will patients in the CC. Statistical analyses for these hypotheses will follow the analytic plan as described for the primary outcomes. Secondary outcomes that are dichotomous (e.g. improved asthma-related quality of life) will be fit using the GEE approach with a logit link, which extends the logistic regression model, as described previously. Outcomes that are continuous (e.g. asthma control, adherence) will be analyzed using the linear mixed-effects model developed by Laird and Ware (1982) which extends linear regression to allow for repeated measurements. Ordinal measures will be estimated as a cumulative odds regression model 138 after satisfying the assumptions of proportionality between levels of the outcome and the explanatory variables. When this assumption cannot be satisfied, nonproportional models, such as logistic regressions between adjacent categories, will be examined.

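### Asthma-related quality of life is classed as a yes/no 'improved' outcome although the hypothesis is about the size of the gain and the items are graded; this costs power whether or not a minimum change is set

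*Protocol*

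**What the plan says.** The secondary hypotheses in section III.7 of the protocol include that intervention subjects will have "greater gains in their asthma-related quality of life". The same paragraph then assigns a model to each type of outcome:

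- Dichotomous: "Secondary outcomes that are dichotomous (e.g. improved asthma-related quality of life) will be fit using the GEE approach with a logit link".
- Continuous: "Outcomes that are continuous (e.g. asthma control, adherence) will be analyzed using the linear mixed-effects model" for repeated measurements.
- Ordinal: a cumulative-odds model, or non-proportional alternatives if its assumption fails.

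On the instrument, section III.6 says "We will use questions about asthma control and quality of life from the National Asthma Survey". The content listed there, which ends with impaired functioning, runs: "including days with symptoms, days symptom-free, emergency room visits, urgent doctor visits, asthma attacks, severity of asthma attacks and the degree to which asthma impairs". On validation, the same section says: "It is not clear how many of these questions are validated". The schedule table in section III.5 shows an 11-item block for asthma control and quality of life at baseline, Cycle 6 and Cycle 13.

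The protocol does not say what counts as improved. It gives no scoring of the items, no minimum change and no rule for subjects already at the best value.

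**The concern.** The plan states a choice here. Quality of life is its named example of a dichotomous outcome, while asthma control and adherence are its examples of continuous ones. Three things count against that choice.

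1. The hypothesis asks how much quality of life rises. The analysis asks what share of subjects rose.
2. The items include day counts and a degree of impairment. A yes/no split discards the graded information already collected at three times.
3. If improvement is judged against the subject's own baseline, a subject at the best value at entry can only be a non-success, the same score as a subject who deteriorates.

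The protocol's own argument also points the other way. It declines to power on change in the Asthma Control Test (ACT) because there is less agreement on a meaningful change than on a cut-off for control. The quality-of-life items have no cut-off in the protocol and, by its own account, uncertain validation, yet they are to be classified by change.

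This is secondary hypothesis (b) in the Specific Aims, and section III.6 even lists quality of life under primary outcome measures. A null result could come from the scoring alone.

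**Working it through.** **1. The plan's own sample size.** Inputs from section III.7: 55% v 70%, two-sided 5%, 80% power, 20% loss.

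n per arm = [1.960·√(2·0.625·0.375) + 0.842·√(0.55·0.45 + 0.70·0.30)]² / 0.15² = (1.342 + 0.570)² / 0.0225 ≈ 162.4, so 163. That is 326 evaluable, and 326/0.80 = 407.5, so 408. Both figures match the protocol. Equal allocation is assumed.

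**2. Assumptions for quality of life.** The protocol gives none, so I take a single normal score with SD 1, 163 per arm, one comparison at 12 months, nobody at the best value, and a baseline-to-follow-up correlation r of 0.4 to 0.84. The upper value is the ACT test-retest figure in section III.6.

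**3. Effect with 80% power in a baseline-adjusted score analysis.** d = (1.960 + 0.842)·√[2(1 − r²)/163]. For r = 0.5, d = 2.802·√(1.5/163) = 0.269 SD.

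**4. The same effect as any improvement.** The SD of change is √[2(1 − r)]. The share improved is 0.50 in the control arm and Φ(d / SD of change) in the intervention arm. For r = 0.5 the SD of change is 1.0 and the shares are 0.500 and Φ(0.269) = 0.606. With the two-proportion formula at 163 per arm:

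Φ{[0.106·√163 − 1.960·√(2·0.553·0.447)] / √(0.500·0.500 + 0.606·0.394)} ≈ 0.485.

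**5. The same effect with a minimum change of 0.5 SD.** The shares are Φ(−0.5 / SD of change) and Φ[(d − 0.5) / SD of change]. For r = 0.5 these are 0.309 and 0.409.

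| r | d (SD) | Shares, any improvement | Power | n per arm for 80% | Shares, 0.5 SD threshold | Power |
|---|---|---|---|---|---|---|
| 0.4 | 0.284 | 0.500 v 0.602 | 46% | 369 | 0.324 v 0.422 | 45% |
| 0.5 | 0.269 | 0.500 v 0.606 | 49% | 345 | 0.309 v 0.409 | 47% |
| 0.7 | 0.222 | 0.500 v 0.613 | 54% | 305 | 0.259 v 0.360 | 50% |
| 0.84 | 0.168 | 0.500 v 0.617 | 57% | 282 | 0.188 v 0.279 | 49% |

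Restoring 80% power for any improvement would take 282/163 = 1.7 to 369/163 = 2.3 times the subjects.

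**6. Baseline adjustment on both sides.** The table adjusts only the score analysis. In simulation with the baseline score also in the logistic model, power was about 53% to 59% for any improvement and 47% to 52% with the 0.5 SD threshold. The score analysis had 77% to 78% in those runs.

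**7. Ceiling, for illustration only.** If 20% of subjects were at the best value at baseline, simulated power was 72% to 75% for the score and 44% to 46% for any improvement with baseline adjustment. If 40% were there, it was 62% to 66% and 29% to 32%. Both ceiling rates are assumed.

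**The case against.** The best reply is that the phrase is only an example in a sentence matching models to outcome types. The definition of improved may sit in a statistical analysis plan that is not shown, so its absence from the protocol is no fault. That stands. It does not rescue the choice, because a threshold leaves power at about 45% to 52% in the same setting.

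It can also be said that a dichotomous example does not exclude an analysis on the scale, since asthma control is analysed both ways. For asthma control, however, the protocol says so. For quality of life it names only the dichotomous form.

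Comparing an adjusted score analysis with an unadjusted split exaggerates the gap. That is right in part: adjusting both narrows it but leaves a clear loss. Even against an unadjusted continuous change score, the efficiency of a median split is 2/π = 0.64, which takes 80% power to Φ(2.802·√0.637 − 1.960) = 61%.

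Three stronger readings are tempting, and the documents support none of them:

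- **A third to a half of subjects would improve by chance alone.** This needs any positive change to count, which the protocol never says, and a fine-grained score. With no true change, simulated shares were 29% to 47% for a score of 11 to 30 levels, 25% to 36% for 7 levels, 12% to 31% for 4 to 5 levels and 2% to 16% for a yes/no item.
- **About half the subjects start at the best value.** The sentence "Our estimated baseline rate of 55% is based on two studies of asthma control" concerns the share controlled on the ACT. It is not a ceiling rate for the quality-of-life items.
- **The GEE fails because improved does not exist at baseline.** Modelling Cycle 6 and Cycle 13 with baseline as a covariate is ordinary practice.

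**Conclusion.** The point holds as a poor choice of analysis for a secondary outcome. The protocol tests a hypothesis about the size of a gain with a yes/no outcome, although the measures are graded and suitable models stand in the same paragraph. In the setting examined, about 80% power falls to about 46% to 59% as any improvement and to about 45% to 52% with a 0.5 SD threshold. Any ceiling would widen the loss.

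These figures rest on a normal score, the stated correlations and a single 12-month comparison, none of which the protocol supplies for this instrument. The direction was the same in every scenario run, but the size is illustrative. Chance improvement arises equally in both arms, so the harm is lost power and an outcome that is hard to interpret. Type I error is unaffected. The sample size rests on ACT control, and the protocol promises no power for quality of life.

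**What to change.** In section III.7, Secondary analyses:

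1. Remove improved asthma-related quality of life as the example of a dichotomous outcome.
2. State that the main quality-of-life analysis is on the original scale at Cycle 6 and Cycle 13, with the baseline value as covariate and the between-arm difference at 12 months as the test. Use the linear mixed model for scores and day counts, and the cumulative-odds model for ordinal items.
3. Keep any responder percentage as supportive only, with a minimum change stated in advance and subjects already at the best value shown separately.

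This is a change of wording. The data are already scheduled at all three times and both models are already in the plan. The cost is that the main result becomes a mean difference or a common odds ratio, which is less immediate to a lay reader than a percentage improved.

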Analysis of main outcome: Data analysis will focus on the primary hypotheses that significantly more subjects in the IC will have their asthma controlled, an Asthma Control Test (ACT) score of ≥ 20, than subjects in the CC. This dichotomized version of the ACT at 12 months is the primary outcome. We considered powering on a numerical change in the Asthma Control Test (ACT), our main outcome measure, but chose not to do this as there is less consensus about what represents a meaningful change in the ACT than there is about what represents appropriate asthma control 5,98. Logistic regression will be used to analyze asthma control at 12 months. Logistic regression allows for inclusion of the two dichotomous strata. Also, it is possible that the groups may have differences at baseline in potential confounders (e.g. socio-economic status, asthma symptoms) that may contribute to group differences in the 12 month event rate between the two conditions. Logistic regression permits inclusion of these potential confounders as covariates. Additionally, as the ACT is measured every 3 months, the logistic regression model can be extended using the generalized estimating equations (GEE) approach of Zeger and Liang (1986) with a logit link so that the repeated measures on each subject can be included in the analyses 137. Thus, asthma control can be examined at any of the preceding time points as well. Tests of the primary hypotheses about intervention effects will be formulated directly in terms of the main effect of intervention. We will also assign a create variables for physicians’ practices, so that physicians who practice together will be given the same variable number. In our analyses we first perform intent-to-treat (ITT) analyses and then will perform analysis including physician- and practice-level variables, while accounting for clustering.

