Analyses of mediating and moderating processes: The analytic procedures outlined provide a convenient way of identifying effect modifiers and confounders, while modeling the underlying relationship of interest. As noted in the analytic plan for the primary outcome, the analysis of moderators will be undertaken by creating interaction terms between treatment and covariates of interest, such as asthma-related quality of life 139, health literacy and socio-demographic characteristics. We will also examine the effects of treatment fidelity and intervention dosage (e.g. number of visits to web site, total time spent on web site) as potential moderators of intervention efficacy. Mediational analyses will be conducted in the form proposed by Baron and Kenny 140. Briefly, this entails four steps in which it is demonstrated that there is: a) a significant association between the independent variable and the dependent variable; b) a significant association between the independent variable and the mediators; c) a significant association between the mediator and outcome; and d) a meditational effect is argued to occur when a significant decrease in the relation between the independent (e.g. treatment) and dependent (e.g. asthma control) variables upon the forced entry of the proposed mediators into the model at the final step. We will examine each mediator separately, as joint estimation makes estimation and interpretation of the effect of each potentially mediating variable problematic. Data for these analyses will be obtained from online surveys, date stamps from the interactive website and from the timing of physician visits from chart reviews. For example, we can test whether use of the interactive website influences use of other asthma controller medications (e.g., salmeterol). However, we will also explore various temporal combinations between the exogenous (treatment), endogenous mediators (asthma specialist visits) and outcomes and we will pay particular attention to the temporal ordering of key events and measurement periods.

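### The four-step mediation plan allows a mediation claim only if the total treatment effect is significant and, on the logistic scale, understates partial mediation

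*Protocol*

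**What the plan says.** Section 7, under the analyses of mediating and moderating processes, names the method: "Mediational analyses will be conducted in the form proposed by Baron and Kenny". Four steps follow. Step (a) is "a significant association between the independent variable and the dependent variable". Steps (b) and (c) require significant treatment-mediator and mediator-outcome associations. Step (d) is the decision rule: "a meditational effect is argued to occur when a significant decrease in the relation between the independent (e.g. treatment) and dependent" variables once the mediator is entered, with asthma control as the example outcome. On the number of mediators per model, the protocol says "We will examine each mediator separately".

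The same section defines asthma control for the main analysis: "This dichotomized version of the ACT at 12 months is the primary outcome", and "Logistic regression will be used to analyze asthma control at 12 months". Its secondary analyses also treat asthma control as continuous: "Outcomes that are continuous (e.g. asthma control, adherence) will be analyzed using the linear mixed-effects model". The mediation paragraph relies on the analyses already outlined and does not say which version it uses.

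Section 6 hypothesises that every listed mediating variable carries part of the intervention effect. The list includes website use before visits, the controller-to-reliever ratio, provider visits, self-management counselling and adherence.

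**The concern.** The trial's rationale is that prompting patients changes the care they receive, and that this care improves control. The mediation analysis is where that chain is examined, and the protocol fixes its decision rule.

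Two features of the rule are doubtful. First, step (a) ties any mediation claim to the significance of the total effect. An indirect effect can be estimated precisely when the total effect is not, because the total effect on a binary outcome is a noisy quantity. Second, odds ratios are non-collapsible. Entering a variable that predicts the outcome moves the treatment log odds ratio away from zero even when nothing is mediated, which works against the fall that step (d) looks for. At stake is a conclusion of no mediation for a process that does carry part of the effect.

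**Working it through.** **Inputs.** From the sample-size text in Section 7: 70% v 55%, two-sided alpha 0.05, 80% power, 408 randomised, 20% loss, 326 analysable, and 940 subjects for a 10-point difference. Assumed: equal allocation (163 per arm), a mediator with unit SD, its shift d under treatment, and its log odds ratio g per SD. The protocol gives no value for d or g, so ranges are shown.

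**1. The protocol's own figures.** Per arm, n = [1.96√(2p̄(1−p̄)) + 0.8416√(p₁q₁+p₂q₂)]² / (p₁−p₂)².
- 70% v 55%: [1.96√0.46875 + 0.8416√0.4575]² / 0.0225 = 162.3, so 163 per arm and 326 in all. 326/0.8 = 407.5, so 408. Reproduced.
- 65% v 55%: 375.6, so 376 per arm and 752 in all. 752/0.8 = 940. Reproduced.

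**2. How often step (a) fails with 163 per arm.** Power = Φ{[Δ − 1.96√(2p̄(1−p̄)/n)] / √((p₁q₁+p₂q₂)/n)}.
- 70% v 55%: (0.15 − 0.1051)/0.05298 = 0.847, power 80.2%. Step (a) fails in about 20%.
- 65% v 55%: (0.10 − 0.1064)/0.05398 = −0.118, power 45.3%. Step (a) fails in about 55%.

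**3. What the requirement costs.** With d = 0.4, the treatment-mediator path has z = 0.4√(163/2) = 3.61 and power Φ(3.61 − 1.96) = 95%. With g = 1.0 the mediator-outcome path is detected in essentially every trial. At 65% v 55% both paths are thus detected in about 95% of trials, but the four steps cannot succeed in more than the 45% that pass step (a). Simulation gives about 44%.

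The table is from 2,500 simulated trials per row, N = 326. Any fall in the coefficient counts as passing step (d), which favours the plan.

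| Rates | g | True share (log-odds scale) | Both paths significant | Four steps |
|---|---|---|---|---|
| 70 v 55 | 1.0 | 100% | 100% | 79% |
| 70 v 55 | 1.0 | 50% | 94% | 76% |
| 70 v 55 | 1.0 | 30% | 56% | 49% |
| 70 v 55 | 2.0 | 50% | 67% | 53% |
| 70 v 55 | 2.0 | 30% | 30% | 20% |
| 65 v 55 | 1.0 | 100% | 99% | 46% |
| 65 v 55 | 2.0 | 100% | 86% | 42% |

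**4. Step (d) on the logistic scale.** Model: logit P(Y=1) = α + c′T + gM, M ~ N(dT, 1), with α and c′ solved so that the marginal rates are 55% and 70%. The unadjusted coefficient is c = logit 0.70 − logit 0.55 = 0.847 − 0.201 = 0.647.

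With no mediation (d = 0), c′ is 0.682, 0.776 or 0.904 for g = 0.5, 1.0 or 1.5: the coefficient rises.

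With d = 0.2, c′ is the d = 0 value minus 0.2g. The apparent share is (0.647 − c′)/0.647. The true share is (0.70 − P₁₀)/0.15, where P₁₀ is the control rate under treatment if the mediator kept its distribution in the control arm.

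| g | c′ | Apparent share | P₁₀ | True share |
|---|---|---|---|---|
| 0.5 | 0.682 − 0.1 = 0.582 | 10% | 0.680 | 14% |
| 1.0 | 0.776 − 0.2 = 0.576 | 11% | 0.664 | 24% |
| 1.5 | 0.904 − 0.3 = 0.604 | 7% | 0.653 | 32% |

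The gap does not come from comparing two scales. On the conditional log-odds scale the true shares are 0.1/0.682 = 15%, 0.2/0.776 = 26% and 0.3/0.904 = 33%.

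The gap narrows as mediation grows: at g = 1.0 and d = 0.5 it is 63% true v 57% apparent. With full mediation c′ = 0 and the apparent share is 100%.

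**The case against.** The method is a named and referenced one, the analysis is explanatory, and effect scale, intervals and covariates are often left to an analysis plan, which is not at hand. One can also argue that an effect should be shown before it is explained. Four narrower points deserve an answer.

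- **No stop rule.** A reader might infer that the plan abandons process analysis when the primary result is null. The text does not say so. It lists what must be demonstrated for a mediation claim, and the secondary analyses test treatment effects on the controller-to-reliever ratio and adherence regardless. What is lost is the formal mediation claim. This stands.
- **Masking at step (d).** A reader might infer from non-collapsibility that the coefficient will usually fail to fall, so that mediation is hidden. The sequence does not support that. With g = 1.0, shifts of 0.1 and 0.2 SD pass step (b) in only about 15% and 44% of trials, and among trials passing (b) and (c) the fall is absent in under 10% and about 1% respectively. In those cases the weak treatment-mediator path is the main limit, and direct estimation would not rescue them. This stands.
- **Mediator strength is assumed.** At g = 0.5 the distortion is small (14% v 10%). This stands, and is why a range is given.
- **The logistic scale is inferred.** The mediation paragraph names no model. With continuous ACT in the linear mixed model the second defect disappears. This stands, but the paragraph does not confine itself to that version.

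None of these removes the first defect. The requirement of a significant total effect is written into the protocol and applies on every scale.

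**Conclusion.** The point holds as two defects of unequal weight in a secondary, mechanistic analysis.

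The main one is step (a). By the protocol's own power it rules out a mediation claim in about 20% of trials at 70% v 55% and about 55% at 65% v 55%, a size of difference that Section 7 accepts may matter clinically. These figures assume equal allocation and 326 analysable subjects. The net loss is largest when mediation is strong and the total effect modest (99% v 46% in the simulation). It is smaller for weak partial mediation (56% v 49%), much of which would be missed anyway.

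The lesser one is step (d). It is conditional on use of the binary outcome under logistic regression, and its size depends on an assumed mediator strength. It understates partial mediation and does not hide full mediation.

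The primary comparison and the sample size are unaffected.

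**What to change.** In the mediation paragraph of Section 7:

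- Remove the requirement of a significant total effect.
- Replace the change-in-coefficient rule with direct estimation of the indirect effect, on one stated scale. For binary control, this could be natural direct and indirect effects as risk differences, from a mediator model and an outcome model. For continuous ACT, it could be the product of coefficients.
- Report bootstrap 95% intervals.
- Adjust for baseline ACT, and for the baseline value of the mediator where it is collected. Section 5 provides baseline counselling questions and two years of earlier claims; website use has no baseline value.
- Keep one mediator at a time, as planned.
- State the assumption of no unmeasured mediator-outcome confounding. It cannot be verified, and the four-step method makes it too.

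The cost is wording and modest programming. No new data are needed.
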